**Methods:**

This study is a single-blinded, multicenter randomized controlled trial. The target sample will consist of 256 community-dwelling non-frail and pre-frail adults of 65 years or older with an increased risk of falls. The intervention group receives the In Balance intervention as it is currently widely implemented in Dutch healthcare, which includes an educational component and physical exercises. The physical exercises are based on Tai Chi principles and focus on balance and strength. The control group receives general written physical activity recommendations. Primary outcomes are the number of falls and fall-related injuries over 12 months follow-up. Secondary outcomes consist of physical performance measures, physical activity, confidence, health status, quality of life, process evaluation and societal costs. Mixed model analyses will be conducted for both primary and secondary outcomes and will be stratified for non-frail and pre-frail adults.

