### Data collection and outcome measures

#### Primary outcome measure

The primary outcome in this study is the number of falls, with or without injuries, assessed with fall diaries and monthly follow-up telephone calls, including questions on the causes, circumstances and consequences of falls. This combination of pro- and retrospective data collection follows guidelines for conducting fall prevention trials [41].

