### Sample size

To obtain a reduction of 50% in the number of falls between the intervention and control group, a minimum of 106 persons are required per group, at a power of 0.80, beta of 0.02 and alpha of 0.05. Taking into account a dropout rate of 20%, the total required sample size is 256 participants. Hence, we expect that about 16 In Balance intervention groups of 8 participants each, are needed to include the required sample size of 128 participants in both the intervention and control group.

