#### Primary and secondary outcomes

The effectiveness of the In Balance intervention in comparison with a control group will be analysed with multilevel mixed model regression analyses for both primary and secondary outcomes. Three hierarchical levels will be included in the mixed models; therapist, participant and time. If necessary, analyses will be adjusted for confounders and stratified for the presence of potential effect modifiers. The primary effect in these analyses is described by the coefficient of the time treatment interaction term. To identify possible differences in intervention effects between non-frail and pre-frail respondents, an a priori subgroup analysis will be performed, stratified for frailty level (non- and pre-frail).

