### Trial status

Enrolment into the study will start on September 1, 2021. We plan to complete the recruitment and data collection at baseline by September 2022, with a 12 months follow-up period on falls incidence and incidence of fall-related injuries until September 2023. This study has been registered with the Netherlands Trial Register on 13 February 2021 (NL9248).

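### For falls, the plan reads the primary effect from the time-by-treatment coefficient, which in a model of counts per interval misses a steady reduction and is not the quantity the trial was sized for

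*Protocol article*

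**What the plan says.** All places are in the protocol article.

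- **Primary and secondary outcomes (statistical analysis).** Effectiveness "will be analysed with multilevel mixed model regression analyses for both primary and secondary outcomes". On structure: "Three hierarchical levels will be included in the mixed models; therapist, participant and time". On the parameter: "The primary effect in these analyses is described by the coefficient of the time treatment interaction term". Falls are not exempted.
- **Primary outcome measure.** Falls are defined and collected as follows: "The primary outcome in this study is the number of falls, with or without injuries, assessed with fall diaries and monthly follow-up telephone calls". The abstract adds: "Primary outcomes are the number of falls and fall-related injuries over 12 months follow-up".
- **Trial status.** After baseline the study continues "with a 12 months follow-up period on falls incidence and incidence of fall-related injuries".
- **Secondary outcome measures.** These are taken at M0, M4 and M12, so they have a value before treatment.
- **Participant characteristics.** Fall history is recorded at M0 and M12 among the descriptive items. Its recall period is not stated, and nothing makes it the baseline value of the primary outcome.
- **Sample size.** "To obtain a reduction of 50% in the number of falls between the intervention and control group", 106 per group are needed at power 0.80 and alpha 0.05, raised to 256 in total for 20% dropout.

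**The concern.** A time-by-treatment term carries a treatment effect when both arms start from a common value before treatment and then diverge. The secondary outcomes fit that pattern. The diary and telephone fall counts do not, because every time point lies after allocation. For such counts the reduction is a difference in level between the arms, and the interaction says only whether that difference changes over the year.

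This decides the main conclusion. Applied literally to counts per interval, the rule could return a null primary result from a trial in which falls were truly halved. The stated power belongs to a different parameter. The same rule covers fall-related injuries and the analyses by frailty level. The economic evaluation, by contrast, uses plain between-group differences in effect, so the two parts of the trial would answer different questions.

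**Working it through.** **1. What the 106 per group was calculated for.** The sample-size section gives no control risk. I assume one-third with at least one fall per year, from the Background. Comparing two proportions, p1 = 1/3 and p2 = 1/6, two-sided alpha 0.05, power 0.80:

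n = [1.96·√(2·0.25·0.75) + 0.842·√(0.2222 + 0.1389)]² / (1/6)² = 105 per group.

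With p1 = 0.33 the result is 107, so 106 is reproduced closely. (Taking the printed beta of 0.02 literally gives 214, so power 0.80 was used.) A rate-ratio formula also comes near for some assumed inputs. With 0.65 falls per year and dispersion 1.0:

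n = (1.96 + 0.842)² · (1/0.65 + 1/0.325 + 2·1.0) / (ln 2)² = 109.

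With 1.2 falls per year and dispersion 2 it gives 107. Every variant that comes close to 106 compares the groups over the year. None contains a time-by-treatment term.

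**2. Where a constant halving sits.** For counts per interval,

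log E(Y) = a + b·time + c·treatment + d·time·treatment.

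A rate ratio of 0.5 in every interval gives c = ln 0.5 = -0.69 and d = 0. This needs no assumed rate or dispersion.

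**3. Power at 106 per arm under a constant rate ratio of 0.5.** Assumptions not in the article: 0.6-1.5 falls per year in controls, gamma variance 1-2, 12 monthly counts, no therapist clustering.

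- *12-month rate ratio, by formula.* The variance of the log rate ratio is (1/r + 2/r + 2k)/106, with r the control rate and k the gamma variance. For r = 0.6, k = 2: 9/106, SE 0.291, and 0.693/0.291 - 1.96 = 0.42, so power is about 66%. For r = 1.5, k = 1: 4/106, SE 0.194, and 0.693/0.194 - 1.96 = 1.61, so power is about 95%.
- *12-month rate ratio, by simulation.* About 68-95% over the same range. Two further cases gave 76% (0.65 per year, dispersion 1.0) and 85% (1.0 per year, dispersion 1.5).
- *Interaction, in simulation.* The mean coefficient over the year was -0.03 and -0.01 in those two cases, with two-sided rejection of 4.8% and 4.4%. Over the full range it favoured the programme significantly in 2-3% of trials.

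**4. If the effect is not constant** (same two cases; the patterns are chosen for illustration).

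- *No effect for 3 months, then halved.* The coefficient is about -0.85 and significant in 27-35%. The overall ratio is (3·1 + 9·0.5)/12 = 0.625, and the 12-month comparison reaches 50%.
- *Ratio rising evenly from 0.25 to 0.75.* The average ratio is 0.50, yet the coefficient is about +1.05 (compare ln(0.75/0.25) = 1.10), the sign of a worsening effect. The 12-month comparison reaches 82%.

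In both patterns the interaction describes the change in the effect and not its size.

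**The case against.** The strongest reply is that the article fixes no distribution, link, time coding or unit of count, and leaves open whether a treatment main effect is included. The zero depends on these choices. With cumulative counts, for example, a constant halving does produce different slopes. The difference is r/24 falls per month, or 0.025 at 0.6 per year and 0.0625 at 1.5 per year. In simulation that slope difference had about 61-93% power. Without a treatment main effect the coefficient is also not zero (about -0.085 per month). It would then describe a steady 0.50 as a ratio sliding from exp(-0.085) = 0.92 in month 1 to exp(-1.02) = 0.36 in month 12.

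This stands to the extent that a reader should not infer that the coefficient is zero under every model. It does not remove the point. No such coding is stated, and counts per interval are a natural reading of monthly calls with time as a level. Nor is this detail left to an analysis plan, because the article itself names the parameter.

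Two other inferences go too far:

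- *That the trial would probably show a significant result against the programme.* This needs a benefit that is strongest early. The intervention section puts education first and starts exercise only in week 5, so a slow onset fits at least as well. The documents establish only that the sign can mislead.
- *That no fall information exists before allocation.* Fall history is asked at M0 and again at M12. It could serve as a covariate, but the plan does not make it time zero of the primary outcome.

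**Conclusion.** Wrong as written. The parameter named for the primary outcome is not the between-group reduction for which the trial was sized. Under a count-per-interval model with a treatment main effect, a constant halving gives a coefficient of exactly zero. Its chance of significance is then about 5% two-sided, against roughly 68-95% for the 12-month rate ratio at 106 per arm. The zero follows from the model alone. The power range rests on the assumed fall rates and gamma variances and ignores therapist clustering, which the planned model includes. The 106 per group is not faulted here: it matches a between-group comparison under plausible inputs. The mismatch is with the analysis sentence.

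**What to change.** In the section on primary and secondary outcomes, state that for falls and fall-related injuries the primary effect is the treatment rate ratio over the 12-month follow-up. It should come from a count model with the log of observed follow-up time as offset, keeping the planned therapist level and with no time-by-treatment term in the primary estimate. Report treatment rate ratios by period as secondary description of onset and fading. Keep the time-by-treatment wording for outcomes measured at M0.

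The cost is one or two sentences. No new data are needed and the sample size does not change. The change should be made before unblinding, because replacing a published primary parameter afterwards would be open to criticism.

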#### Secondary outcome measures

Besides the number of falls and fall-related injuries, positive effects on physical functioning, physical activity, quality of life and other self-reported outcome measures are measured [42]. The secondary outcome measures will be assessed at three time points during the study period; at entry of the study (baseline, M0), after 4 months to determine the short-term effects (M4) and after 12 months to determine the long-term effects (M12). Societal costs will be assessed at M4, after 8 months (M8) and M12. All secondary outcomes are listed in Table 2 and are described in detail below.

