An additional strength of this study is that we do not only take falls and fall-related injuries into account, which have a large impact on the individual and healthcare, but we will also investigate multiple secondary outcomes such as physical functioning, physical activity, quality of life and other self-reported outcome measures [18]. Despite the health benefits of physical activity, the paradoxical increase in exposure to fall risk should also be taken into account when evaluating falls prevention interventions [67]. Although this study is not powered for the secondary outcome measures, analysis of these outcomes will nevertheless provide insights that are useful to gain more knowledge about the underlying mechanisms of the In Balance intervention on a potential reduction of falls and fall-related injuries. For example, physical activity improves balance control and muscle and bone strength and thus is expected to decrease the number of falls and fall-related injuries [68–71].

This study also includes a process evaluation, to collect information that will be relevant for further implementation of the intervention. Not part of this protocol, but additionally to the process evaluation, we consider focus groups with participants of the intervention group, therapists and other stakeholders to obtain facilitating and hindering factors for implementation. These factors can be taken into account when implementing the outcomes of the study described in this research protocol.

Several challenges of this study need to be mentioned as well. First, the inclusion of 256 participants in this trial, both non-frail and pre-frail, will be challenging. For recruitment, we will involve therapists and their local network over diverse neighbourhoods. Due to the COVID-19 situation, the inclusion of sufficient participants will be extra challenging. We expect that participants may be reticent when considering participating in the In Balance intervention, although the majority of our target population is expected to be vaccinated at the start of our study. Moreover, the social component of the In Balance intervention can be a facilitating factor to participate in this study. In a recent inventory among several In Balance therapists on conducting the In Balance intervention in times of COVID-19, therapists indicated that the In Balance intervention can be conducted while taking the COVID-19 measures into account.

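### Secondary outcomes: fitted with a free treatment main effect, the time-by-treatment coefficient is a change-from-M0 contrast, less precise than using M0 as a baseline

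*Protocol article*

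**What the plan says.** Under Statistical analysis, Primary and secondary outcomes, the protocol article states that effectiveness "will be analysed with multilevel mixed model regression analyses for both primary and secondary outcomes". It then says: "Three hierarchical levels will be included in the mixed models; therapist, participant and time". The effect itself is defined in one sentence: "The primary effect in these analyses is described by the coefficient of the time treatment interaction term". On covariates it says only: "If necessary, analyses will be adjusted for confounders and stratified for the presence of potential effect modifiers". The M0 value of the outcome is not named as a covariate, and the fixed effects are not listed.

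The section Secondary outcome measures fixes the visits: "The secondary outcome measures will be assessed at three time points during the study period; at entry of the study (baseline, M0"), with M4 and M12 as the other two. One outcome differs: "Societal costs will be assessed at M4, after 8 months (M8) and M12".

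**The concern.** With visits at M0, M4 and M12, the role of M0 decides what the time-by-treatment coefficient means. If M0 were only a covariate, the interaction would show how the effect differs between M4 and M12, which is not the effectiveness that the section sets out to estimate. The natural reading is therefore that M0 is one of the outcome time points.

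In the ordinary interaction model, with main effects of time and of treatment, each arm has its own M0 mean. The coefficient is then the between-arm difference in change from M0. M0 is measured before the intervention in randomised arms, so the true M0 means are equal by design. Estimating them separately adds noise to the contrast. It also pushes the estimate in the opposite direction to any chance difference at M0.

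At stake is the precision of the secondary results. The Discussion says "Although this study is not powered for the secondary outcome measures", yet it looks to these outcomes for insight into how the intervention might work. The analysis is also repeated by frailty level. With a target of 30–50% pre-frail and 102 completers per arm, that stratum holds about 31 to 51 completers per arm (102 × 0.3 and 102 × 0.5), so avoidable loss is felt more there.

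**Working it through.** The article gives no precision or power figure for the secondary outcomes, so there is nothing of its own to reproduce. The check compares two ways of using the same data.

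**Inputs**
- 128 per arm randomised and 20% dropout (Sample size), so 128 × 0.8 = 102 per arm at follow-up.
- r, the correlation between M0 and follow-up: not in the article, assumed and varied.
- Outcome scaled to SD 1 at each visit; therapist-level variation left out.

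**Complete data, n per arm**
- Change contrast: variance = 4(1 − r)/n.
- Baseline-adjusted contrast: variance = 2(1 − r²)/n.
- Ratio, adjusted to change: (1 + r)/2. Information lost by the change contrast: (1 − r)/2.

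| r | ratio | loss |
|---|---|---|
| 0.3 | 0.65 | 35% |
| 0.5 | 0.75 | 25% |
| 0.6 | 0.80 | 20% |
| 0.7 | 0.85 | 15% |
| 0.9 | 0.95 | 5% |

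An exact generalised least squares calculation for M0, M4 and M12 with a random intercept gives the same ratios for the M12 coefficient. A simulation of 5000 trials with 106 per arm gave 0.735, 0.788 and 0.852 at r = 0.5, 0.6 and 0.7. If time enters as a linear term in months, the loss is 22%, 17% and 12.5% at the same three values.

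**With the planned dropout**

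In a mixed model with M0 in the outcome vector, participants lost after M0 still contribute their M0 value. With N = 128 at M0 and n = 102 at M4:
- Free M0 means: variance = 2[(1 − r²)/n + (1 − r)²/N].
- Common M0 mean: variance = 2(1 − r²)/n.

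Power below is two-sided at 0.05 for an illustrative difference of 0.3 SD, which is not a figure from the article.

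| r | SE, free M0 means | SE, common M0 mean | loss | power, free | power, common |
|---|---|---|---|---|---|
| 0.5 | √(2[0.75/102 + 0.25/128]) = 0.136 | √(1.5/102) = 0.121 | 21% | 0.59 | 0.70 |
| 0.6 | √(2[0.64/102 + 0.16/128]) = 0.123 | √(1.28/102) = 0.112 | 17% | 0.69 | 0.76 |
| 0.7 | √(2[0.51/102 + 0.09/128]) = 0.107 | √(1.02/102) = 0.100 | 12% | 0.80 | 0.85 |

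**Chance imbalance**

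With complete data and a chance M0 difference d, the change contrast shifts by −(1 − r)d. One standard error of the M0 difference at 102 per arm is √(2/102) = 0.14 SD, so at r = 0.6 the shift is 0.4 × 0.14 = 0.056 SD.

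**If the treatment main effect is left out**

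Both arms then share one M0 mean, the time-by-treatment coefficient already has the smaller variance, and the loss is zero.

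**The case against.** The strongest reply is that the sentence defining the effect contains no error. A model with a common M0 mean also reports a time-by-treatment coefficient, so the text fits the efficient model as well as the inefficient one. The loss arises only from a free treatment main effect, which the article neither states nor rules out. The article is also a condensed account; the list of fixed effects may sit in a full protocol or analysis plan that is not shown, and its absence here is not a fault. All of this stands, and it is why the point is conditional. What remains is that the ordinary form of the stated model is the less precise one, nothing in the text steers away from it, and the M0 values that would recover the loss are already collected.

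A reader might infer that the plan wastes 15–25% of the information on its secondary outcomes. The documents do not support that as a statement of fact. The range assumes r between 0.5 and 0.7 and complete data. A highly repeatable measure would lose less, and under the planned dropout the figures at those correlations are lower. Nor does it cover every secondary outcome: societal costs have no M0 value, and the economic evaluation uses linear regression.

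A reader might also infer bias. Randomisation keeps the change contrast unbiased over repeated allocations; the issue is precision, and sensitivity to the imbalance in the one trial that is run. Finally, the article claims no power for these outcomes, so no stated power is missed.

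**Conclusion.** The point holds conditionally. For secondary outcomes measured at M0, M4 and M12, if the model is fitted with a free treatment main effect, the stated coefficient is a difference in change from M0. It is valid but less precise than an analysis that uses M0 as a baseline, for any r below 1. For an illustrative 0.3 SD difference under the planned dropout, that amounts to 5 to 10 percentage points of power for r between 0.7 and 0.5. The sizes rest on an assumed r, equal variances at each visit, a continuous outcome and no therapist-level variation. There is no loss if a common M0 mean is what the investigators intend.

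Priority is low to moderate. Only secondary outcomes are affected; the primary outcome, the number of falls during follow-up, is outside this point.

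**What to change.** For each continuous secondary outcome with an M0 value, fix one of two forms in the analysis section:
- keep M0 in the outcome vector and constrain both arms to a common M0 mean (time plus time-by-treatment at M4 and M12, no treatment main effect); or
- model M4 and M12 only, with the M0 value as a covariate and treatment contrasts at each visit.

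In either case, report the M4 and M12 treatment contrasts. The two forms are equivalent for continuous outcomes with complete data. They differ when M0 values are missing: the covariate form drops those participants unless a rule for missing M0 values is set, so the constrained form is simpler there.

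The cost is one sentence, with the same data and software and no added measurement. If a common M0 mean was always intended, the sentence only makes that explicit.

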### Recruitment, randomization, blinding and treatment allocation

Recruitment will be done via flyers, advertisements in local papers, folders distributed through supermarkets, pharmacists, community centres, general practitioners, at annual flu shots, and via personal invitations by In Balance therapists and general practitioners. Participants will be randomized into the intervention group or the control group using block-randomization to balance the size of the two groups. Randomization will be stratified according to frailty. We aim to include 30–50% of the participants in the pre-frail subgroup and 50–70% in the non-frail subgroup in both the intervention and control group. As soon as one of the subgroups starts to outnumber the other subgroup, we will only target the underrepresented subgroup for recruitment. Two hundred fifty-six sealed envelopes in blocks of 10 (5 envelopes per group) will be prepared by an independent investigator. These sequentially numbered envelopes contain a random computer-generated unique identification number. A second matching envelope contains the group information. All investigators and assessors involved in this study will be blinded to group assignment until completion of statistical analyses. Due to the nature of this study, participants and therapists cannot be blinded to group allocation. Participants will be informed orally about their allocation and therapists will receive the names of those participants who will participate in the In Balance intervention.

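### The plan asks whether the effect differs by frailty, but names only separate analyses per stratum and no comparison between them

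*Protocol article*

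**What the plan says.** The Primary and secondary outcomes section first describes multilevel mixed models comparing intervention with control, and defines the effect of interest: "The primary effect in these analyses is described by the coefficient of the time treatment interaction term". It then turns to frailty: "To identify possible differences in intervention effects between non-frail and pre-frail respondents, an a priori subgroup analysis will be performed, stratified for frailty level". No treatment by frailty term, or other comparison of the two stratum effects, is named there. The aim at the end of the Background and the Discussion also speak only of stratifying by frailty.

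The abstract puts it more broadly: "Mixed model analyses will be conducted for both primary and secondary outcomes and will be stratified for non-frail and pre-frail adults".

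Frailty is also a randomisation stratum, with planned shares given under Recruitment, randomization, blinding and treatment allocation: "We aim to include 30–50% of the participants in the pre-frail subgroup and 50–70% in the non-frail subgroup in both the intervention and control group". The Sample size section addresses the whole trial only. For a halving of falls it states: "a minimum of 106 persons are required per group, at a power of 0.80, beta of 0.02 and alpha of 0.05". It mentions no subgroup.

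**The concern.** The stated purpose is to find differences in effect, while the stated means is one analysis per frailty group. These answer different questions. One significant and one non-significant result is not evidence that the effects differ, because the gap can come from limited numbers in each stratum alone.

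The stakes are practical. Frailty status is part of the study aim, and the Discussion lists stratification as a strength because it shows the programme's impact in its different target groups. The article expects health insurers to use the results when deciding on coverage. It also reports that the programme was rolled out on the strength of a favourable finding in one frailty subgroup of an earlier trial. A mistaken conclusion that only one group benefits could therefore change who is offered the programme.

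**Working it through.** **Inputs.** From the Sample size section: a 50% reduction (rate ratio 0.5), 106 per group, power 0.80, alpha 0.05 (two-sided assumed, as the article does not say), 20% dropout, 256 in total. From the recruitment section: a pre-frail share f of 0.30 to 0.50 in both arms.

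**The plan's own figure.** The article gives no control-group level. If one-third of controls fall at least once a year (the Background's general figure, used here as an assumption) and this is halved to one-sixth, the pooled two-proportion formula gives 105 per group, against 106 stated. Then 106 × 1.2 = 127.2, rounded up to 128 per group and 256 in total, as stated. The steps below need only the stated 80% overall power, not this route to it.

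**Size of the strata.** On 106 evaluable per arm, the pre-frail stratum has 0.30 × 106 ≈ 32 to 0.50 × 106 = 53 participants per arm.

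**Power within a stratum.** At 80% power the overall standardised effect is 1.96 + 0.84 = 2.80. If information is proportional to headcount, a stratum with share f has 2.80 × √f, so its power is Φ(2.80√f − 1.96). With stratum powers p1 and p2, the probability that exactly one is significant is p1(1 − p2) + p2(1 − p1). With the same true 50% reduction in both strata:

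| Pre-frail : non-frail | Power, pre-frail | Power, non-frail | Exactly one | Both | Neither |
|---|---|---|---|---|---|
| 30:70 | 0.34 | 0.65 | 0.55 | 0.22 | 0.23 |
| 40:60 | 0.43 | 0.58 | 0.51 | 0.25 | 0.24 |
| 50:50 | 0.51 | 0.51 | 0.50 | 0.26 | 0.24 |

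For 30:70, for example: 0.335 × 0.350 + 0.650 × 0.665 = 0.55.

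**Sensitivity of the exactly-one figure.**
- 102 per arm (128 less 20%): 0.50–0.55. 128 per arm with no dropout: 0.49–0.55.
- Overall power 50%: 0.41–0.42. 65%: 0.47–0.50. 90%: 0.47–0.54.
- Overall power 98%, if the printed beta of 0.02 is taken literally (it does not match power 0.80): 0.31–0.42.
- Negative binomial simulation (4,000 trials per scenario, shares 30:70 and 50:50, assumed control rates 0.5–0.9 per year and dispersion 0.25–1.5): 0.49–0.55.

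**Testing the difference instead.** Under a common effect, an interaction test at alpha 0.05 declares a difference in about 5% of trials (4.6–5.6% in the simulation). Its power is limited:
- The standard error of the overall log rate ratio is ln 2 / 2.80 = 0.247.
- The standard error of the difference between strata is 0.247 × √(1/f + 1/(1 − f)), which is 0.495 at f = 0.5 and 0.540 at f = 0.3.
- Power for a two-fold ratio of rate ratios is 0.29 at f = 0.5 and 0.25 at f = 0.3.
- The ratio needed for 80% power is exp(2.80 × 0.495) ≈ 4.0 at f = 0.5 and exp(2.80 × 0.540) ≈ 4.5 at f = 0.3.

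**The case against.** The strongest reply is that the error is partly imputed. The article does not say that p-values will be compared or that each stratum will be judged at p < 0.05. Stratum estimates with confidence intervals fit its wording, and effects per target group are a legitimate aim in themselves. This stands in part: the 50–55% figure describes a common way of reading such results, not a rule the plan sets.

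A reader might infer that stratified analyses can never test a difference. That goes too far. The two estimates are independent and could be contrasted afterwards with a simple z-test. The supported statement is that the plan does not say this will be done.

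A reader might also infer from the abstract that the stratified analyses are the main ones. The methods text does not support this. It describes the overall comparison first and calls the frailty analysis a subgroup analysis, so the abstract is loosely worded and out of line with it.

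It can be argued that an interaction test is a detail for an analysis plan that is not shown. That plan may indeed contain one. But the article does more than leave a gap: it names a question and assigns it a method that does not answer it. The general provision to stratify by effect modifiers where necessary does not help, as it names no test of modification and the frailty analysis is not conditional on one.

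Finally, an interaction test has so little power here that the trial can hardly identify differences either way. This is correct. The gain is mainly protection against over-reading the strata.

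**Conclusion.** The point holds in limited form. The method named for the frailty question does not match the purpose given for it, because no comparison between strata is specified. If the strata are read by separate significance, about half of trials with a common effect would show a benefit in only one group, against about 5% false positives for a direct test of the difference.

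The size rests on four assumptions: two-sided p < 0.05 in each stratum, a true 50% reduction in both, overall power of 80%, and information proportional to headcount. The last implies similar fall rates in the two strata, for which the article gives no figures. The result is fairly stable when overall power is moved between 50% and 90%, and smaller (31–42%) at 98%.

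The overall comparison of intervention with control is not affected. The plan should be changed on this point, but it does not undermine the trial's main result.

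**What to change.** 1. State that the analysis of all participants, adjusted for the frailty stratum, is the primary analysis.
2. Add a treatment by frailty contrast to that model, for the primary effect as the plan defines it. If that remains the time by treatment coefficient, the contrast is how that coefficient differs between frailty strata. For falls modelled on a log-rate scale, report the ratio of rate ratios with its 95% CI.
3. Label this contrast exploratory and give the reason: the trial was not sized for it.
4. Report non-frail and pre-frail effects as estimates with CIs, without separate claims of significance.
5. Align the abstract sentence with the methods text, so that stratification by frailty is described as a subgroup analysis.

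The cost is one model contrast and some wording. Frailty is already measured at baseline and used in randomisation, so recruitment and data collection do not change. The price is more modest subgroup conclusions: a wide interval for the difference will often be all the trial can offer on this question.
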